## Abstract

**Background:**

Different dietary protein sources are supposed to have various effects on metabolic responses and arterial stiffness in the postprandial period. This study aims to assess the postprandial effects of dietary protein sources, including animal-based protein (AP) and plant-based protein (PP), as part of a high-protein breakfast on appetite response, energy metabolism, and arterial stiffness in overweight and obese men.

**Methods:**

This acute randomized crossover clinical trial will be conducted at the Persian study research center at Imam Reza Hospital, affiliated with the Mashhad University of Medical Sciences, located in the northeast of Iran. Forty-six healthy overweight, and obese men aged 18–60 years will be enrolled based on the eligibility criteria. The subjects will complete two interventions (high-protein AP and PP meals) with 1 week washout period. The primary outcome will be the acute effect of the two test meals on appetite response, energy metabolism parameters, including resting metabolism rate (RMR), diet-induced thermogenesis (DIT), and substrate oxidation (SO), and arterial stiffness indices, including pulse wave velocity (PWV) and pulse wave analysis (PWA). The secondary outcomes include changes in lipemia, glycemia, and insulinemia.

**Discussion:**

The findings of this study will provide novel insight regarding the acute effects of different protein sources on energy metabolism, appetite, and arterial stiffness as a significant cardiovascular disease (CVD) risk factor. It will help dieticians develop effective and efficient meal plans to improve weight reduction and maintenance in overweight/obese individuals.

**Trial registration:**

Iranian Registry of Clinical Trials; code: IRCT20211230053570N1; registered on February 10, 2022

**Supplementary Information:**

The online version contains supplementary material available at 10.1186/s13063-023-07374-1.

## Background

Overweight/obesity is a significant public health problem [1]. The prevalence of overweight/obesity is rapidly increasing at an alarming rate in most parts of the world and is estimated to affect about 20% of the adult population by 2030 [1]. Complex mechanisms have been shown to lead to obesity; however, it is mainly the result of an imbalance between energy intake and energy expenditure [2, 3]. Several studies on the obesogenic and metabolic effects of dietary macronutrients have shown that dietary macronutrient composition can play a pivotal role in energy metabolism and body weight adjustment [4].

It is well documented that dietary protein increases thermogenesis in the postprandial period after meal ingestion. The reason is that the energy cost of the process of digestion, absorption, and metabolization of the protein (23%) is more than that of fat (3%) and carbohydrate (6%) [5]. In addition to thermogenic effects, protein suppresses appetite and energy intake through various mechanisms [6–8]. Therefore, high-protein diets (≥ 25% energy) are suggested to increase weight loss, maintain muscle mass, and prevent weight regain [9, 10].

Regardless of protein quantity, proteins have unique properties associated with the source of protein, amino acid composition, and digestive and absorption kinetics. So, it is suggested that different dietary protein sources exhibit diverse acute and chronic effects on thermic and metabolic responses and appetite control [11–15].

Some studies have shown that animal-based proteins (APs) have greater satiating effects compared to plant-based proteins (PPs) [6, 13, 16]. This difference can be related to the difference in amino acid composition, digestion and absorption rate, protein structure (which influences the digestion and absorption rate), and postprandial incretin hormone responses to APs and PPs [17].

Moreover, based on the results of acute phase studies, different dietary proteins may differently affect energy metabolism markers, for example, energy expenditure (EE), diet-induced thermogenesis (DIT), and substrate oxidation (SO) [11, 12, 18]. Mikkelsen et al. compared the postprandial effects of pork meat and soy protein on 24-h energy expenditure (EE) and found that AP (pork meat) induced a 2% higher EE than PP (soy) [12].

Different dietary protein sources have also been shown to have various effects on lipid and glucose levels in the postprandial period [19]. This difference may be due to the different insulinotropic impacts of protein sources [19]. Some studies have demonstrated that AP ingestion, as a breakfast meal, leads to less significant postprandial changes in the plasma levels of insulin and glucose [20, 21]. In addition, some studies have shown that consuming a diet enriched with APs leads to lower postprandial lipemia by decreasing triglyceride (TG) or free fatty acids levels compared to PPs [22–24].

Postprandial hyperglycemia [25] and hypertriglyceridemia [26] have emerged as independent risk factors of cardiovascular disease (CVD), promoting interest in the cardiovascular effects of postprandial dietary exposure. It has been shown that postprandial lipemia causes acute changes in vascular endothelial function due to increased oxidative stress, which affects arterial stiffness [27]. Arterial stiffness is a measure of vascular function that is strongly associated with CVD risk [28]. Pulse wave velocity (PWV) is the gold standard method, which measures the propagation velocity of pressure waves (m/s) [29]. A research in this regard indicated that high-fat meals lead to a blood pressure-dependent increase in PWV and a decrease in arterial wave reflection [30]. However, data are scarce regarding the effects of dietary protein source on postprandial arterial stiffness.

### Study rationale

According to the above content, it seems that different dietary protein sources have different postprandial effects on metabolic responses, appetite control, and vascular function. However, minor and inconclusive information is available on the difference in postprandial effects between APs and PPs. Therefore, this study was designed to evaluate the postprandial effects of dietary protein source (AP vs. PP) on the mentioned markers in overweight and obese men. We did not include women in the study due to the potential effect of the menstrual cycle on metabolism. On the other hand, to have a more homogeneous population, we only included overweight and obese men in the study. To the best of our knowledge, this is the first study to assess the postprandial effect of dietary protein source on arterial stiffness.

### Study objectives

#### Primary objectives

The primary objective is to evaluate the postprandial effects of dietary protein source (AP Vs. PP) as part of a high-protein breakfast on appetite response, energy metabolism parameters, including resting metabolism rate (RMR), DIT, and SO, and arterial stiffness indices, including PWV and pulse wave analysis (PWA), in overweight and obese men.

#### Secondary objectives

The secondary objective is to evaluate the effects of dietary protein source (AP vs. PP) on postprandial lipemia, glycemia, and insulinemia in overweight and obese men.

### Trial design

This is an acute randomized crossover clinical trial study of two protein-based breakfast meals with different protein sources (AP and PP). Each participant will consume two different test meals on different days with a 1-week washout period in between. Figure 1 shows the diagram of enrollment, intervention, and assessments.

**Fig. 1 Fig1:**
[figure not shown]
Study diagram of enrollment, interventions, and assessments

Participants will be instructed not to drink alcohol or engage in severe physical activity within 48 h before each test day. Participants will not be allowed to fast the day before the test days. On the morning of the test day, participants will travel to the research center at Imam Reza Hospital by taxi (with a minimum activity) to arrive at 7 a.m. Participants should abstain from food, drinks (except water), alcohol, and caffeine for 12 h.

On arrival, anthropometric parameters will be measured, and an intravenous catheter will be inserted into an antecubital arm vein. Before consuming the test meals, fasting measurements of indirect calorimetry (IC), PWV and PWA, and subjective appetite will be performed, and venous blood will be collected via the intravenous catheter. Then, participants will be given 15 min to eat the test meals under the researcher’s supervision until the test meal is wholly consumed.

Afterward, postprandial phase tests, including IC, PWA, PWV, and assessing the appetite response, will be performed. Blood samples will also be collected within 6 h. All the tests will be performed in the same conditions (e.g., quiet and temperature-regulated room).

Figure 2 depicts the schedule of the study days. Time points were determined according to the preliminary results of our previous study. The testing conditions will be repeated on the next test day.

**Fig. 2 Fig2:**
[figure not shown]
Scheduling study days. Asterisk symbol (*) indicates the following: the exact sequence of measurements at the times points are as follows: (1) blood sampling, (2) appetite assessment, and (3) calorimetry

The study protocol was written based on the Standard Protocol Items: Recommendation for Interventional Trials (SPIRIT) Checklist (Table 1).

**Table 1 Tab1:** Schedule of enrolment, intervention, and assessment based in the Standard Protocol Items Recommendations for Interventional Trials (SPIRIT) guidelines

**Time point**	**Study period**				
	**Enrollment**	**Allocation**	**Post-allocation**		
	**Pre-intervention**	**Time 0**	**baseline**	**Intervention visit 1**	**Intervention visit 2**
**Enrolment**	✓				
Eligibility screening	✓				
Informed consent	✓				
Allocation		✓			
**Interventions**					
AP				✓	✓
PP				✓	✓
**Data collection**					
International physical activity questionnaires		✓			
24-h dietary recall		✓			
Anthropometric parameters		✓			
Body composition		✓			
**IC**					
RMR		✓	✓	✓	✓
SO		✓	✓	✓	✓
DIT		✓	✓	✓	✓
RQ		✓	✓	✓	✓
**Velocimetry**					
cBP		✓	✓	✓	✓
HR		✓	✓	✓	✓
AIx		✓	✓	✓	✓
PWV		✓	✓	✓	✓
PWA		✓	✓	✓	✓
**Laboratory assessment**					
Lipid profile (TG, LDL, HDL, TC, and FFAs)		✓	✓	✓	✓
Serum glucose		✓	✓	✓	✓
Serum insulin		✓	✓	✓	✓

*AP* animal-based protein, *PP* plant-based protein, *IC* indirect calorimetry, *RMR* resting metabolic rate, *SO* substrate oxidation, *DIT* diet-induced thermogenesis, *RQ* respiratory quotient, *cBP* central blood pressure, *HR* heart rate, *AIx* augmentation index, *PWV* pulse wave velocity, *PWA* pulse wave analysis, *TG* triglycerides, *LDL* low-density lipoprotein, *HDL* high-density lipoprotein, *TC* total- cholesterol, *FFA* free fatty acids

## Methods: participants, interventions, and outcomes

### Study setting

This randomized crossover study will be conducted at the Persian study research center at Imam Reza Hospital, affiliated with the Mashhad University of Medical Sciences, located in the North-East of Iran. Participants will be recruited through advertising with posters or email at the Mashhad University of Medical Sciences.

### Eligibility criteria

#### Inclusion criteria

Participants must meet all the following inclusion criteria to participate in this study: men aged 18–60 years old, body mass index (BMI) between 25 and 35 kg/m^2^, being apparently healthy (based on the individual’s self-report and medical history), willing to undertake the required fasting periods, and provision of written consent.

#### Exclusion criteria

The exclusion criteria are as follows: professional athletes; current smoking habits; history of CVDs, hypertension, diabetes mellitus, hyperlipidemia, neurological and/or neuropsychological disorders, and renal disorders, use of medications or supplements that affect energy and protein metabolism (e.g., thyroid medications, supplements containing l-carnitine, ephedrine, caffeine, and antidepressant drugs), use of protein supplements, any supplements for weight loss or weight gain; use of medications or supplements affecting appetite, consumption of toxic substances, history of more than 10% body weigh change within the past 6 months, history of irregular breakfast consumption (less than 5 times a week), having dietary restrictions, fear of getting blood drawn (trypanophobia), inability to partake in the intervention due to intolerance/dietary preferences, and objective diagnosis of hypertension, diabetes mellitus, or hyperlipidemia based on the participant’s biochemical and blood pressure data after they are recruited in the study**.**

### Who will take informed consent?

The eligible participant will be informed by the principal researcher. Written and verbal information regarding the study will be provided to the participants in an easy and understandable language. Then, written consent will be obtained from participants following the trial standard operating processes. Participants will not be included in the study if they decline to give written consent or show substantial distress.

### Additional consent provisions for collection and use of participant data and biological specimens

Contents of the consent form include agreement upon data usage in case of participants’ withdrawal from the study and permission for sharing relevant data with specific academic experts from the universities collaborating in the trial or with other regulatory authorities (Ethic number: IR.MUMS.MEDICAL.REC.1400.399).

### Interventions

#### Explanation for the choice of comparators

In the present study, we aimed to compare two intervention conditions, including AP and PP conditions, and there is no control condition.

#### Intervention description

Intervention condition A: participants will receive an AP test meal. The test meal will provide 20% of the calculated total daily energy requirements and will consist of 30% protein (from animal sources), 40% carbohydrate, and 30% fat.

Intervention condition B: participants will receive a PP test meal. The test meal will provide 20% of the calculated total daily energy requirements and will consist of 30% protein (from plant sources), 40% carbohydrate, and 30% fat.

To estimate the total daily energy requirements of the subjects, the Harris–Benedict Eq. [31] will be used as follows:For women—BMR = 655.1 + (9.563 × weight in kg) + (1.850 × height in cm) − (4.676 × age).For men—BMR = 66.5 + (13.75 × weight in kg) + (5.003 × height in cm) − (6.75 × age).

After calculating BMR by the above formula, TEF and physical activity will be added to calculate TEE.

The test meals will be prepared in the Nutrition Department kitchen at the Mashhad University of Medical Sciences, Mashhad, Iran. The composition of the test meals is presented in Table 2. Two test meals will be isocaloric and similar in macronutrient and fiber content. The palatability of the test meals will be measured using the visual analog scale (VAS). The viscosity of the meals will be measured using a Brookfield Synchro-Lectric Viscometer (Brookfield Engineering Laboratories, Inc.).

**Table 2 Tab2:** Ingredient composition of the test meals

	**AP**	**PP**
**Protein source**	Chicken breast, egg, yogurt	Soy protein
**Other ingredients**	White toast, potato, carrot, pickled cucumber, parsley, sunflower oil	White toast, mushroom, bell pepper, onion, tomato paste, sunflower oil

*AP* animal-based protein, *PP* plant-based protein

#### Criteria for discontinuing or modifying allocated interventions

No particular side effects are expected following the test meals in the present study. The possible reasons for stopping the intervention will be the occurrence of any intervention or measurements-related side effects. The Ethics committee of Mashhad University of Medical Sciences (MUMS) will decide on the referred cases.

#### Strategies to improve adherence to interventions

The strategies considered to improve the adherence of the participants to the intervention include; preparing meals in accordance with Iranian culture and taste, measuring the palatability of the test meals using VAS, and careful monitoring of participants during the intake of test meals.

#### Relevant concomitant care permitted or prohibited during the trial

This trial includes no relevant concomitant care.

#### Provisions for post-trial care

A physician and nurse will be present, and the participants’ symptoms will be checked during the project (6 to 8 h). After removing the catheter, blood pressure, puncture site bleeding, and other symptoms, such as dizziness, will be checked.

### Outcomes

The primary outcome of this trial will be the comparison of the acute effects of the two test meals on appetite response, and energy metabolism parameters, including resting energy expenditure (REE), DIT, and SO, and arterial stiffness indices (PWV and PWA) in overweight and obese men.

The secondary outcome is to compare the effects of two test meals on postprandial lipemia, including free fatty acids (FFA), low-density lipoprotein (LDL), high-density lipoprotein (HDL), total cholesterol (TC), and triglycerides (TG), glycemia (blood glucose), and insulinemia (serum insulin) in overweight and obese men.

### Participant timeline

The time schedule of enrolment, interventions, and assessments is shown in Table 1.

### Sample size

The sample size was calculated concerning the primary outcomes observed in our previous study and considering desired power of 80% and 95% confidence interval. Considering the mean and standard deviation for the difference in REE of 250 and 330 kcal/day, respectively, an average correlation of 0.5, and a possible dropout rate of 10%, the sample size was calculated as 46 participants (23 participants in each group).$${\varvec{m}}=\frac{{2\left({{\varvec{z}}}_{1-\frac{\boldsymbol{\alpha }}{2}}+{{\varvec{z}}}_{1-{\varvec{\beta}}}\right)}^{2}\boldsymbol{ }{{\varvec{\sigma}}}^{2}[1+{\varvec{n}}(1-{\varvec{\rho}})]}{{{\varvec{n}}{\varvec{d}}}^{2}}\boldsymbol{ }=\boldsymbol{ }\frac{{2\left(1/96+0/84\right)}^{2}\times {330}^{2}\times [1+4(1-0.5)]}{4{(250)}^{2}}=21\simeq 23$$

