## Data collection and management

### Plans for assessment and collection of outcomes

#### Indirect calorimetry

RMR (kcal/d), DIT (kcal/d), and SO (g/d) will be measured by IC. To do calorimetry, participants will be asked to lie down in the supine position while awake and immobile; then, air samples will be collected using a mask (MetaLyzer 3B-R3 device), and respiratory gas (O_2_ and CO_2_) exchange will be measured for 20 min in the fasting phase, followed by postprandial measurements 60, 180, and 300 min after consumption of the test meals. The IC will be calibrated before the start of the measures.

The respiratory quotient (RQ) is the ratio of VCO_2_ to VO_2_ (VCO_2_/VO_2_), which reflects the rate of SO. DIT is the production of heat related to SO during energy uptake. DIT varies according to the quantity and type of oxidized substrate (i.e., carbohydrates, proteins, and fat).

IC will be performed in a quiet area at room temperature and mild lighting and require specific conditions (i.e., free of physical activity and psychological stress, fasting state for more than 6 h before the measurement, and resting in the supine position for > 20 min before the calorimetry). During the measurement, the room temperature will be maintained between 23 and 25 °C.

Given that stress has a negative effect on the quality of the calorimetry, the following measures will be taken to minimize the stress level of the participants:Performing the test in a completely quiet roomProviding facilities for the participants to rest in the intervals between assessments and at least half an hour resting before the testIn case of determining stress and tension in participants, testing will be postponed to another day

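### The sample-size formula sizes two independent groups with an invalid correlation term, so the stated 80% power at 250 kcal/day is not the power of this 46-man crossover

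*Protocol article*

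**What the plan says.** The Sample size section takes its inputs from the team's previous study: "Considering the mean and standard deviation for the difference in REE of 250 and 330 kcal/day, respectively, an average correlation of 0.5", with 10% dropout, "considering desired power of 80% and 95% confidence interval". It prints the formula m = 2(z_a+z_b)^2 sigma^2 [1+n(1-rho)]/(n d^2), substitutes n = 4 and rho = 0.5, obtains 21, raises this to 23, and concludes that "the sample size was calculated as 46 participants (23 participants in each group"). It does not define n, and it does not say whether rho relates time points within a visit or the two meals.

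The Trial design section describes a crossover: "Each participant will consume two different test meals on different days with a 1-week washout period in between". The Sequence generation section confirms that only the starting meal is randomised. Calorimetry is done once fasting, "followed by postprandial measurements 60, 180, and 300 min after consumption of the test meals".

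The section on statistical methods for primary and secondary outcomes names three things: independent two-sample t tests between conditions, a repeated-measures mixed model, and a carryover rule. As written, that rule leads to a first-period parallel comparison when carryover is not significant.

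**The concern.** Three features of the calculation do not fit the trial.

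- **Correlation factor.** It moves in the wrong direction. More highly correlated readings carry less information, yet the printed requirement falls as rho rises.
- **Two-group structure.** The leading 2 sigma^2, and the solution per group that is then doubled, treat the men as two independent samples. In a crossover the variance that matters is that of the within-man difference between meals, and the answer is a total number of men.
- **Meaning of 330.** The text presents it as belonging to a difference ("mean and standard deviation for the difference in REE of 250 and 330 kcal/day, respectively"), but the formula doubles its square as if it were the SD of one group.

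REE is among the primary outcomes and is the only one used for sizing. A reader will take 250 kcal/day as the limit of what 46 men can detect with 80% power. That is not what the design delivers under a paired analysis, nor under the parallel comparison that the methods section also allows.

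**Working it through.** **Inputs, all from the Sample size section:** z values 1.96 and 0.84; d = 250; sigma = 330; rho = 0.5; n = 4; dropout 10%. Not given: the meanings of n and rho, whether 330 refers to the within-man difference or to one reading, and the between-meal correlation (called r below).

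**1. The plan's own figure.**
2 x (1.96+0.84)^2 x 330^2 x [1+4(1-0.5)] / (4 x 250^2) = 2 x 7.84 x 108,900 x 3 / 250,000 = 20.49, rounded to 21. For dropout, 21 x 1.1 = 23.1 and 21/0.9 = 23.3; the plan takes 23 and doubles it to 46. The figure reproduces (strict rounding up would give 24 and 48).

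**2. The correlation factor.** The mean of n equally correlated readings has variance sigma^2 [1+(n-1)rho]/n. Two checks on the printed factor:

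- At n = 1, rho must drop out, giving m = 2 x 7.84 x 108,900/62,500 = 27.3. The printed factor gives 54.6 at rho = 0 and 41.0 at rho = 0.5.
- At n = 4:

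| rho | printed m | valid m |
|---|---|---|
| 0 | 34.2 | 6.8 |
| 0.5 | 20.5 | 17.1 |
| 1 | 6.8 | 27.3 |

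With only this term corrected (2.5 in place of 3), the two-group answer is 17.1, so 18 per group.

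**3. The crossover.** The total is N = (z_a+z_b)^2 SD_D^2/d^2, where SD_D is the SD of the within-man difference. With SD_D = 330: 7.84 x 108,900/62,500 = 13.7, so 14 men, or 16 by the noncentral t distribution. Completers: 46 x 0.9 = 41.4, so about 41. If 330 is instead the SD of one reading, SD_D = 330 x sqrt(2(1-r)). By noncentral t with 41 men:

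| Reading of 330 | SD_D | Power at 250 | 80%-power difference (kcal/day) |
|---|---|---|---|
| SD of the difference, or one reading with r = 0.5 | 330 | 99.7% | 148 |
| One reading, r = 0.25 | 404 | 97% | 181 |
| One reading, r = 0 | 467 | 92% | 209 |

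The normal approximation gives slightly smaller differences, for example 2.8 x 330/sqrt(41) = 144. Averaging readings lowers them too: for a mean of four readings correlated 0.5 within a visit, with no correlation between meals, SD_D = 330 x sqrt(2 x 0.625) = 369 and the last row's 209 becomes about 166.

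**4. A two-group comparison.** If the analysis falls back to the first period, or independent t tests are applied to two separate groups of 20 to 21 completers, power at 250 kcal/day is:

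- one reading, SD 330: about 65 to 67%;
- mean of three or four readings at rho = 0.5, SD 330 x sqrt(2/3) = 269 or 330 x sqrt(0.625) = 261: about 82 to 86%.

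An independent t test on all 41 values per meal has standard error 330 x sqrt(2/41), the same as the r = 0 row, so power of about 92% if the values really were uncorrelated. None of these routes gives 80% as a consequence of the printed calculation.

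**The case against.** The strongest reply is that the methods section names independent t tests and, read literally, makes a first-period parallel comparison the usual route. A two-group formula would then match the analysis. That stands as a limit on the paired figures: 99.7% and 148 kcal/day require a within-man analysis and SD_D of 330. It does not rescue the calculation. The carryover rule looks reversed, the same section also plans a repeated-measures mixed model, and the correlation factor is invalid under any of these analyses.

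Second, 330 comes from a study that is not shown, so its meaning cannot be settled from the protocol. This is fair, and it is why a range is given rather than one figure.

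Third, 23 in each group can be read as 23 per sequence, since the starting meal is randomised 1:1. This is acceptable as wording, but it does not justify the factor 2 or the doubling.

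Fourth, the arithmetic is right and 46 men exceed the need of a paired analysis. Both are true. The fault is in the choice of formula, and a null REE result would in any case be read mainly from its confidence interval.

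A reader might infer that n = 4 is itself a mistake, because only three calorimetry readings follow the meal. The protocol never defines n. That it counts the fasting reading is an assumption, and a repeated-measures model could legitimately include that reading as a time level.

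**Conclusion.** The concern holds. The printed correlation factor is invalid (17.1 with the valid one, against 20.5), the structure is that of two independent groups, and the SD is used differently from how it is described. The stated 80% power at 250 kcal/day with 46 men is therefore not a property of the crossover.

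For a paired analysis with about 41 completers, power is 92% to 99.7% and the 80%-power difference about 209 to 148 kcal/day. This assumes a non-negative between-meal correlation of up to 0.5, or that 330 already is the SD of the within-man difference. For a two-group comparison with 20 to 21 men per group, power is about 65 to 67% for one reading and 82 to 86% for a mean of three or four.

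Two stronger readings are not supported. One is that the trial is underpowered for REE: in a paired analysis the error is conservative. The other is that 14 to 16 men would suffice: that holds only if 330 is the SD of the within-man difference (or one reading's SD with r = 0.5), the analysis is paired, and there is no dropout. The documents do not establish the first two, and the plan allows for 10% dropout.

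**What to change.** Keep 46 men. In the Sample size section:

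- Replace the formula with N total = (z_a+z_b)^2 SD_D^2/d^2, with a t correction.
- State whether 330 is the SD of the within-man difference or of one reading. If it is of one reading, give the between-meal correlation.
- Define n and rho. If readings are averaged, use [1+(n-1)rho]/n.
- Change the per-group count to 23 expected per sequence, or delete it.
- Report the power at 250 kcal/day and the 80%-power detectable difference between meals for about 41 completers under the paired analysis.

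In the statistical methods section, name that same paired analysis, so that the power statement and the test refer to one comparison.

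The cost is one rewritten paragraph and a matching sentence in the methods. Enrolment and conduct do not change.
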